### Intervention

#### The mindful living with challenge (MLWC) intervention

Participants in the intervention group are required to follow the developed WeChat small program by scanning the QR code, and then receive the online MLWC intervention. The MLWC intervention will be developed by two psychiatrists, and one of them has been certified in the Training of Mindfulness Facilitation program at the Mindful Awareness Research Center of University of California, Los Angeles (UCLA). The MLWC intervention adopts some elements from mindfulness-based stress reduction and Mindful Awareness Practices, and includes mindfulness meditation and mindful stretching as core components. A similar intervention has been successfully used on attention monitoring and acceptance in pregnant women in China [19]. Through a series of mindfulness training courses, participants are hypothesized to increase their ability to regulate their emotions and learn to observe the physical pain and psychological frustration caused by COVID-19 infection with equanimity. The purpose of the study is to help participants improve their skills in coping with psychological symptoms, improve their quality of life during recovery, and prepare to return to a normal life.

The MLWC intervention will involve internet-based mindfulness training conducted in six weekly courses of two sessions a week and 0.5 h per session, which focus on the four important parts of MBI: attention control, self-awareness, acceptance and discernment, and relating to difficult thoughts/emotions. Two new sessions of online lessons will be updated weekly in six weeks. The study participants are expected to spend an average of 1 h per week viewing each lesson, which consisted of a theoretical instrument, some meditation practices, and homework in the form of audio and video. Participants will be required to perform formal/informal mindfulness practice at home for 5 min daily initially, advancing to 20 min daily at the end of the intervention period, and to record or report their difficulties and progress during the practice. To enhance adherence, push notifications from the WeChat small program will be sent to participants daily to remind them about their weekly attendance and regular practice. See Table 2 for the context of the MLWC intervention.

**Table 2 Tab2:** The content of mindful living with challenge (MLWC) intervention

Session	Theoretical instrument	Meditation practice	Homework
1	Explanation of the 5 facets of mindfulness (i.e. describing, acting with awareness, non-judging, and non-reacting), and of the importance of the mindfulness practices which is a means to attention control, how can we incorporate mindfulness into daily life, previous application and scientific findings of mindfulness based interventions	Mindful eating practice, mindful breathing meditation	Participants will be asked to conduct daily life mindfulness practices and mindful breathing meditation for 5–10 min daily for 7 days a week Participants will also be asked to record and provide feedback on any difficulties and their experience during the training
2	Explanation of the brain’s mode of action and being, thoughts/emotions/body feeling Instructing participants to talk to their bodies, relieve the pain and pressure in the healing process. Recognize the pain and try to persuade themselves to accept it, and realize self-awareness in the process	Mindful body scan practice, three-minute breathing space practice	Participants will be asked to conduct mindful body scan practice, three-minute breathing space practice, and filling in pleasant/unpleasant experiences calendar for 10–15 min daily for 7 days a week respectively Participants will also be asked to record and provide feedback on any difficulties and their experience during the training
3	Introduce the scientific understanding of sleep, sleep hygiene education, and seven attitudes of practicing mindfulness	Sitting meditation (mountain meditation and mindful sleep meditation)	Participants will be asked to conduct sitting meditation and mindfulness clock for 15 min daily for 7 days a week respectively Participants will also be asked to record and provide feedback on any difficulties and their experience during the training
4	Introduce mindful living with thoughts, using the **‘**STOP’ and ‘RAIN’ principle to dealing with a storm of thoughts and emotions	Mindful walking meditation, sitting meditation (lake meditation)	Participants will be asked to conduct mindfulness listening practice, mindfulness movement, and STOP/ RAIN practice for 15–20 min daily for 7 days a week respectively Participants will also be asked to record and provide feedback on any difficulties and their experience during the training
5	Introduce mindful movement for relaxing body and mind. Explanation of identification of avoidance response, allowing and letting it go	Mindful yoga practice	Participants will be asked to conduct sitting meditation for 15 min daily for 7 days a week and practice mindful yoga three times a day as appropriate Participants will also be asked to record and provide their feedback on any difficulties and their experience during the training
6	Introduce tired funnel and how to balance our daily life, mindful living with a challenge, and how to live a mindful life, live in the present	Sounding meditation; loving and kindness meditation	Participants will be asked to list nourishing/consuming activities and weave their own mindfulness parachute Participants will be encouraged to engage in various mindfulness practices on a daily basis in the future Participants will be asked to complete the post-program questionnaire and give feedback on the content, form, and organization of the intervention

#### Control group

Participants in the waitlist control group will receive the full 12-session online MLWC intervention upon completion of all treatment procedures by the intervention group after the 3-month follow-up survey.

## Measures

### Adherence

Participants will be informed of the importance of attending each session and required to complete the homework, as the effectiveness of the MLWC intervention on mental health and quality of life is dependent on adherence. Adherence to the intervention was examined through documentation of completed sessions. Firstly, the internet-based intervention platform can automatically record which participant has logged into each session and how much time they spend on mindfulness training per week. In addition, participants will be reminded to complete their homework after completion of each session. Moreover, the post-program questionnaire will be sent to the participants at the end of the intervention to ask about their adherence issues.

### Outcome measurements

All scales to be used in this study are validated Chinese version.

#### Primary outcome: PTSD, depression, anxiety and peace of mind

The psychological impact of COVID-19 will be assessed by the 22-item Impact of Event Scale-Revised (IES-R). IES-R is composed of three subscales and aims to measure the mean avoidance, intrusion, and hyperarousal (Cronbach's α = 0.80) [23–25]. Depression symptoms will be assessed by the 9-item Patient Health Questionnaire (PHQ-9) (Cronbach's α = 0.86) [26–28]. The level of general anxiety will be assessed by the 7-item Generalized Anxiety Disorder Questionnaire (Cronbach's α = 0.89) [29, 30]. Additionally, the 7-item Peace of Mind Scale developed by Lee et al. will be used to measure the peace of mind, one part of the well-being in the Chinese culture (Cronbach's α = 0.90) [31, 32].

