In view of the current epidemic situation and the corresponding prevention and control requirements, internet-based interventions can provide an alternative to face-to-face therapy in enhancing mental health and quality of life for patients with COVID-19. Internet-based healthcare has enabled patients with a variety of geographical distance to receive the same therapy and get benefits from the same interventions, such as digital cognitive behavioural therapy for insomnia [14–16]. This form of psychotherapy can provide treatment and intervention efficiently to patients under the requirements of social distancing during the COVID-19 epidemic [14]. Mindfulness-based intervention (MBI) is an approach that focuses on the cultivation of conscious awareness, and orientation towards the present moment with curiosity and openness, which has been shown helpful in the treatment of mental health [17–20]. Unlike behavioral therapy, which involves relaxation techniques and changing the schedule of daily activities, mindfulness-based interventions help patients cope with anxiety and depression by enhancing their ability to manage stress and reducing negative coping behaviors, hence are more adaptive and persistent [20]. Especially when combined with the web-based technology, mindfulness-based intervention can benefit patients who are infected and treated in isolation wards, and those who are quarantined with no access to psychotherapy as well. [17, 20] An internet-based integrated intervention including some mindfulness skills on depression and anxiety symptoms in Chinese patients with COVID-19 has demonstrated that patients of the intervention group exhibited significantly decreased levels of depression and anxiety symptoms in comparison with those of the control group over a 2-week study period [18].

In the mainland of China, WeChat App and its small programs have dominated the browsing time of mobile phone users [21] Given the emerging need for psychological rehabilitation among COVID-19 survivors recently, this randomized controlled trial will be conducted in this population to examine the effectiveness and feasibility of a 6-week Mindful Living With Challenge (MLWC) intervention focusing on mental health and quality of life via WeChat. We hypothesized that the training could enhance the physical and mental health at post-program and 3-month follow-up.

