### Study objectives

The primary study objective of this study is to assess the efficacy of the MLWC intervention on PTSD, depression, and anxiety among COVID-19 survivors. The secondary study objective is to investigate the effects of the MLWC intervention on fatigue and sleep quality among COVID-19 survivors. The exploratory objective is to determine how mindfulness training affects mental health and quality of life among COVID-19 survivors and to evaluate the possible mediators and moderators (mindfulness, stillness, nonattachment, resilience and perceived social support) of the link between the MLWC intervention and target outcomes.

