### Sample size

A priori power analysis has been conducted on the statistical software G*Power 3.1.9.2 (Heinrich-Heine-Universität Düsseldorf). The trial between the MLWC intervention group and the control group will be tested superiority in promoting mental health status at a superiority margin of 10%. Thus, with a 1:1 allocation to each group and allowing for a 40% attrition rate, at least 1600 participants will be recruited (power = 0.9, α = 0.05, two-tail).

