### Data collection, management, and monitoring

Data will be collected at baseline (one week before the intervention), post-intervention (one week after the last session of MLWC), and at 3-month of follow-up. The questionnaire comprises structured and open-ended questions about mental health status, quality of life, and satisfaction with the program. Demographics will be collected at baseline, including age, employment status, education level, marital status, and other information.

Electronic questionnaires powered by the REDCap software will be used to collect data, hence there will be no formal data monitoring committee. Survey questions filled up by the participants will be automatically uploaded to the read-only web-based database to ensure the authenticity of the data. Moreover, our researchers will promptly check the collected data after each questionnaire survey.

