### Statistical analysis

IMB SPSS Statistics 22.0 (IBM Corp., Armonk, NY, USA) will be used to process data and conduct a *t*-test, chi-square test, and correlation analysis. Analyses will be conducted based on an intention-to-treat approach, and two-sided with *P* < 0.05 will be considered statistically significant. Quantitative data accords with normal distribution will be described as mean ± standard deviation (*SD*), and qualitative data will be expressed as the number (percentage). Student’s *t*-test and the chi-square test will be employed to examine between-group differences in the baseline. The repeated measures ANOVA will be used to compare the scores for the six instruments, and the paired-samples *t*-test will be used to test for within-group differences. We will also conduct a correlation analysis to test the associations between variables in pre-program and post-program in each group. Structural Equation Model will be conducted to explore the interaction of the variables.

Furthermore, in order to elaborate on the meaning of the relationship between the mindfulness training and the outcome variables of mental state and quality of life among COVID-19 survivors, an analysis of mediator or moderator effects will be conducted and some more in-depth information about the research may be explained. We will use the hierarchical multiple regression analyses to test how or why some facets of mindfulness may take a role in our outcomes.

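### The primary objective names three outcomes and the outcome section four, and a single unadjusted 5% threshold covers them with no rule for what counts as success

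*Protocol article*

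**What the plan says.** Three parts of the protocol article bear on which outcomes are primary.

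- Study objectives: the primary objective is to "assess the efficacy of the MLWC intervention on PTSD, depression, and anxiety among COVID-19 survivors". Peace of mind is not named there, nor among the secondary objectives (fatigue, sleep quality) or the exploratory ones.
- Outcome measurements: the heading reads "Primary outcome: PTSD, depression, anxiety and peace of mind", and the text assigns one scale to each: IES-R, PHQ-9, GAD-7 and the Peace of Mind Scale.
- Table 1 lists the same four scales under primary outcome measures.

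On the error rate, the Statistical analysis section sets one criterion for the analyses: "two-sided with *P* < 0.05 will be considered statistically significant". On the model it says: "The repeated measures ANOVA will be used to compare the scores for the six instruments". The six are apparently the four primary and two secondary scales. It does not say which effect or visit is decisive.

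On timing, the Background hypothesises that the training could "enhance the physical and mental health at post-program and 3-month follow-up". Data are collected at baseline, "post-intervention (one week after the last session of MLWC), and at 3-month of follow-up". Neither follow-up visit is called primary.

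The Sample size section uses one set of error rates ("power = 0.9, α = 0.05, two-tail") for an undefined mental health status, so it does not single out one scale either.

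**The concern.** There are two linked problems.

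First, the document gives two different primary sets. A favourable result on Peace of Mind alone would be a primary success under the outcome section and Table 1, yet it would not answer the primary objective. Condensing a protocol into an article does not explain the conflict, and an analysis plan could settle it only by overriding one of the sections.

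Second, the Discussion plans a general conclusion, that the programme is efficacious for mental health and quality of life. Several primary scales feed that conclusion, each read against the same 5% threshold. If success on any one of them were taken as enough, the error rate of the general claim would exceed the 5% used for the sample size. Leaving the rule open until results are seen would also let the choice of scale or visit follow the data.

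**Working it through.** **Inputs from the protocol article.** Primary scales: 4 (outcome section, Table 1) or 3 (Study objectives). Threshold: 0.05 two-sided. Follow-up visits: 2. Sample size: at least 1600, 1:1, 40% attrition, power 0.90. Evaluable: 1600 × 0.6 = 960, or 480 per arm.

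**Inputs assumed.** (a) Any one significant primary scale counts as efficacy. (b) Correlation between scales is 0.3 to 0.8. (c) Correlation between the two visits is 0.5 or 0.7. The document gives none of these.

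**The plan's own figure.** The article states no family-wise error rate to reproduce. The 1600 cannot be strictly reproduced, because neither a control rate nor an SD accompanies the 10% margin. It can be approached: 30% against 40% gives 954 evaluable and 954 / 0.6 = 1590, and a standardised difference of 0.21 also gives 1590.

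**Error rate, one test per scale.** For k independent tests at 0.05, the chance of at least one false positive is 1 − 0.95^k.

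- k = 3: 1 − 0.8574 = 14.3%
- k = 4: 1 − 0.8145 = 18.5%

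With correlated scales (simulated equicorrelated normal statistics, 1,000,000 draws, global null):

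| Correlation between scales | Any of 4 at 0.05 |
|---|---|
| 0.3 | 17.4% |
| 0.5 | 15.6% |
| 0.7 | 13.0% |
| 0.8 | 11.4% |

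For the objective's three scales, the figures are about 12.5% at 0.5 and 11.0% at 0.7.

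**Upper case, both visits tested separately.** With k = 8 independent tests, 1 − 0.95^8 = 33.7%. With correlated scales and visits it runs from 29.8% (scales 0.3, visits 0.5) down to 18.4% (scales 0.8, visits 0.7). The Statistical analysis section does not literally plan these eight tests.

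**Opposite case, all four scales must succeed.** Under the global null the error is about 1.0% at correlation 0.8 and smaller at lower correlations. No such rule is stated either.

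**Cost of adjusting.** The document gives no standardised effect, so one is back-solved from 480 per arm and 90% power: d = (1.960 + 1.282) × √(2/480) = 0.209. The expected test statistic is then 0.209 × √(480/2) = 3.238. Approximate power is Φ(3.238 − z).

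| Threshold | z | Power per scale |
|---|---|---|
| 0.05 | 1.960 | 0.90 |
| 0.05/3 = 0.0167 | 2.394 | 0.80 |
| 0.05/4 = 0.0125 | 2.498 | 0.77 |

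The thresholds 0.0167 and 0.0125 are the strictest Holm step with three and four scales; later steps are less strict. On a different assumed basis, 50% against 40% with 480 per arm, power falls from 88% at 0.05 to 73% at 0.0125.

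**The case against.** The 5% sentence is a general threshold in a condensed article. The testing order, any adjustment and the success rule are commonly left to the full protocol or analysis plan, neither of which is shown. Nothing in the article says that one significant scale would prove efficacy. If all four scales had to succeed there would be no inflation at all.

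This objection stands in part. Silence on an adjustment method would not be a finding by itself, and the any-one-suffices rule is an assumption that must be labelled as such. It does not dispose of the point: the article itself names two different primary sets and applies one threshold across them, and an unseen document cannot make both sets right.

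A reader might infer more: that four scales at two visits are each tested at 5%, so that any of eight results may be claimed as the primary success with an error rate near 34%. The document does not support this. It plans a repeated measures ANOVA for the instruments, with no separate test at each visit, so 34% is the extreme of an upper case.

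A reader might also assume that a baseline-adjusted model would make up the lost power. The article does not plan such a model. With d = 0.209 and 480 per arm, regaining 0.90 at a threshold of 0.0125 would need a baseline correlation above roughly 0.5, which the article does not give.

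**Conclusion.** The point holds in limited form and should be fixed. The conflict between the primary objective (three outcomes) and the outcome section with Table 1 (four) is a plain contradiction and needs no assumption.

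The inflation is conditional. If one significant primary scale is read as efficacy, the chance of a false-positive primary is about 11% to 19%, against a nominal 5%. That range covers four tests, from a correlation of 0.8 to independence. Separate testing at both visits would raise it to about 18% to 34%, but the text does not plan that. Within the assumed range the conclusion is robust: even four scales correlated at 0.8 give more than twice the nominal rate. An adjustment in a document not shown could remove the inflation, but not the contradiction.

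**What to change.** 1. Make Study objectives, the outcome section and Table 1 name the same primary set. Either keep IES-R, PHQ-9 and GAD-7 as primary and list Peace of Mind as secondary, or add Peace of Mind to the primary objective. Both reconcile the text; the choice is the sponsor's.
2. In Statistical analysis, name the between-group contrast from the repeated measures model, and the time point, that decide each primary comparison.
3. Apply Holm across the primary scales at two-sided 0.05. Label all other P values as secondary or exploratory.

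Naming a single primary scale and time, or fixing a testing order, would also hold the error at 5% without raising the sample size.

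The cost is wording plus some power per scale: at the back-solved effect of about 0.21, from 0.90 to about 0.80 (three scales) or 0.77 (four) at the strictest Holm step. The Settings section says the study had not been carried out at submission. The change belongs before outcome data are seen, because a primary scale or visit chosen afterwards would not be credible.

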#### Secondary outcomes: fatigue and sleep quality

Fatigue scale-14 (FS-14) assesses the patient's level of physical fatigue and mental fatigue (Cronbach's α = 0.81) [33, 34]. The 19-item Pittsburgh Sleep Quality Index (PSQI) assesses respondents’ sleep disturbances during the past month (Cronbach's α = 0.84). [35, 36] PSQI can be divided into seven component scores: subjective sleep quality, sleep latency, sleep duration, habitual sleep efficiency, sleep disturbances, use of medication, and daytime dysfunction [35].

#### The possible mediators and moderators: mindfulness, nonattachmet, stillness, resilience and perceived social support

The mindfulness level will be assessed by the 20-item short formed Five Facets of Mindfulness Questionnaire (FFMQ-SF). FFMQ-SF is a self-reported questionnaire with five mindfulness domains: observing, describing, acting with awareness, non-judgment, and non-reactivity (Cronbach's α = 0.86) [37, 38]. Nonattachment will be evaluated by the 7-Item Nonattachment Scale (NAS-7) (Cronbach's α = 0.82) [39–41]. To measure the extent to which participants experience stillness, the 11-item Stillness Scale will be used. It is developed and validated by one of the authors with three subscales: tranquility, concentration, and equanimity. (Cronbach’s α ranges from 0.72 to 0.75). In addition, participants' resilience will be measured by the 17-item Resilience Style Questionnaire (RSQ) (Cronbach’s α = 0.88) [42]. The level of emotional and material social support that participants receive will be measured with two items used in previous studies (Cronbach’s α = 0.68) [43].

### Data collection, management, and monitoring

Data will be collected at baseline (one week before the intervention), post-intervention (one week after the last session of MLWC), and at 3-month of follow-up. The questionnaire comprises structured and open-ended questions about mental health status, quality of life, and satisfaction with the program. Demographics will be collected at baseline, including age, employment status, education level, marital status, and other information.

Electronic questionnaires powered by the REDCap software will be used to collect data, hence there will be no formal data monitoring committee. Survey questions filled up by the participants will be automatically uploaded to the read-only web-based database to ensure the authenticity of the data. Moreover, our researchers will promptly check the collected data after each questionnaire survey.

